# **A Randomized, Controlled Trial on Diet, Insulin Sensitivity, and Postprandial Metabolism**

## **Summary**

This randomized, controlled trial aims to elucidate the mechanisms by which a plant-based dietary intervention causes weight loss. Using a low-fat, plant-based diet for 16 weeks, along with an untreated control for comparison, the study will measure changes in insulin sensitivity, postprandial metabolism, and intracellular lipid, and assess their associations with changes in body weight.

### **1. SPECIFIC AIMS AND OVERVIEW**

#### **1.1. Specific Aims**

**Specific Aim 1.** This study tests the hypothesis that weight changes associated with a low-fat plant-based diet are, in part, the result of increased postprandial metabolism (thermic effect of food).

**Specific Aim 2.** This study tests the hypothesis that increased postprandial metabolism in response to a diet intervention is the result of increased insulin sensitivity.

**Specific Aim 3.** This study conducts a pilot substudy to test the hypothesis that changes in insulin sensitivity observed in response to a diet intervention correlate with changes in intramyocellular and/or intrahepatocellular lipid.

#### **1.2. Protocol Overview**

In a 16-week trial, overweight adults will be randomly assigned to two groups. Changes in insulin sensitivity, postprandial metabolism, and body weight will be the primary dependent variables.

The Diet Group will be asked to follow a low-fat, vegan diet and will receive weekly classes and support.

The Control Group will be asked to make no changes in diet or exercise for 16 weeks, but will be instructed in the intervention diet at the study's conclusion.

## **2. BACKGROUND AND SIGNIFICANCE**

Excess body weight is a major contributor to many health problems, including diabetes, cardiovascular disease, orthopedic problems, and certain forms of cancer. In epidemiologic studies, individuals following vegan diets tend to have significantly lower body weights, compared with individuals following other dietary patterns. In studies of overweight individuals, the adoption of a low-fat plant-based diet predictably reduces body weight, even in the absence of any specified limitation on energy intake.

The mechanisms by which plant-based diets reduce body weight are not entirely clear. Previous studies have identified two possible explanations: First, to the extent that vegan diets are low in fat and high in fiber, they have a relatively low energy density, which reduces energy intake. Second, a low-fat vegan diet may increase postprandial metabolism (the thermic effect of food). These observations suggest that the diet leads to weight loss by (1) reducing energy intake and (2) increasing postprandial energy output.

A prior study including 64 overweight postmenopausal women randomly assigned to a low-fat vegan diet or a comparison diet based on the guidelines of the National Cholesterol Education Program for 14 weeks found that the vegan diet led to significantly greater weight loss (5.8 kg for the vegan group, compared with 3.8 kg for the comparison group). The vegan diet group also had a 16% increase in postprandial metabolism and an increase in insulin sensitivity that was significant within group, although not between groups. However, because the comparison group used an active diet and there was no untreated control group, that study was not able to show the degree to which a plant-based diet influences energy expenditure, compared with untreated participants.

Insulin resistance has been shown to be related to fat accumulation within muscle cells (intramyocellular lipid) and liver cells (intrahepatocellular lipid). The above findings suggest the possibility that low-fat, vegan diets reduce the quantity of lipid stored within these cells, which, in turn, improves insulin sensitivity.

Some evidence suggests that the accumulation of intracellular fat may be responsive to diet. In a 2012 study at Yale University, 7 lean, young individuals who were known to be insulin-resistant and who had parents with type 2 diabetes underwent a hypocaloric (1200 kcal/d) diet for 9 weeks, leading to an average weight loss of  $4.1 \pm 0.6$  kg. During this intervention period, average intramyocellular lipid fell approximately 30%, from  $1.1 \pm 0.2\%$  to  $0.8 \pm 0.1\%$ .

High-fat diets appear to downregulate the genes required for mitochondrial oxidative phosphorylation in skeletal muscle and increase intramyocellular lipid. In contrast, a case-control study found that soleus muscle intramyocellular lipid concentrations were significantly lower in a group of 21 vegans, compared with 25 omnivores.

In research studies, the acceptability of plant-based diets appears to be similar to that of other therapeutic diets over both the short and long term, as indicated by rates of retention, diet adherence, and diet acceptance questionnaires. If a plant-based diet increases postprandial metabolism, its use for the prevention and management of weight disorders and related health problems will have a more solid rationale. This is especially important given that weight problems are widespread and there is a great deal of confusion among the public regarding which diet method to select.

### **3. RESEARCH DESIGN, RECRUITMENT, AND ASSESSMENTS**

#### **3.1. Overview of Research Design**

In a randomized, controlled trial, we will test the effects of a low-fat, plant-based diet on insulin sensitivity, postprandial metabolism, and body weight in overweight adults over a 16-week period, using for comparison an untreated control. A substudy will examine effects on intracellular lipid.

### **3.3. Recruitment and Screening Procedures**

Volunteers will be recruited through notices placed in waiting rooms of physicians' offices, letters sent to patients of medical practitioners, and advertisements placed in newspapers, on radio, and in buses in the Washington, DC, area, as well as social media postings. (**Appendix 1**)

Volunteers' initial calls will be directed to PCRM, where research staff will screen participants using a telephone screening script (**Appendix 2**). Research staff will explain the study, review participation criteria, and inquire about other motivations for volunteering, filling out a paper interview screening form for each person who calls. Volunteers who satisfy the participation criteria will be scheduled for group and/or individual information sessions. The names/identifiable information of volunteers who do not satisfy participation criteria will be destroyed (shredded) immediately. For these individuals, the research team will retain only de-identified demographic information and the reason for exclusion, for purposes of evaluating participation statistics.

At the group and/or individual information sessions (some volunteers may attend individually; others may be seen in groups), the investigators and research staff will explain the study and its scientific basis in detail and review participation criteria in simple, nontechnical terms. They will also provide instruction on filling out a diet record. Additional content will be determined by questions raised by volunteers, and may relate to study logistics, the recruitment process, the content of the vegan diet and ease of following it, clinical assessments, or the weekly classes. To protect patient privacy, volunteer names will not be used at these meetings. Volunteers will have a chance to ask questions about the study and the informed consent process in private, and each volunteer will meet in private with study personnel at the conclusion of the group session, even if he or she has no questions. Volunteers who choose to complete the informed consent document (**Appendix 3**) will also be asked to complete a contact information form (**Appendix 4**) and a general medical history form (**Appendix 5**). Volunteers will be assigned identification numbers in the order in which they complete the informed consent document. These numbers will be used in place of identifying information for purposes of data collection, assessment, and analysis. During the

screening process, prospective volunteers will be provided the study coordinator's phone number and contact information in order to be able to reschedule and cancel their appointments, if necessary.

Prospective volunteers will then be asked to complete a practice 2-day dietary record to demonstrate their ability to track nutrient intake for research purposes. A letter will be sent to the participants to remind them to complete their 2-day diet record with instructions (**Appendix 6**). When completed, these records will be reviewed for completeness by a registered dietitian.

Volunteers who have completed the informed consent process and practice dietary records and meet the study participation criteria will be asked to schedule individual appointments for baseline assessments. There, they will be asked to fill out new 3-day dietary records. Volunteers can either submit questionnaires online, print, scan and email them, or send them through regular mail. Those who satisfactorily complete the baseline assessments and 3-day dietary records will be enrolled in the study.

The cost of all tests and procedures will be covered by PCRM. If any examination or test reveals that a participant has a medical condition that requires additional diagnostic tests or treatment, research staff will advise the participant of that fact, but will not provide such additional diagnostic tests or treatment. There is no cost for the weekly group sessions. Parking will be free during participants' visits to the PCRM office for assessments, meetings, and group sessions.

### **3.4. Inclusion and Exclusion Criteria**

Inclusion criteria are as follows:

1. Men and women age  $\geq 18$  years of age
2. Body mass index 28-40 kg/m^2

Exclusion criteria are as follows:

1. Diabetes mellitus, type 1 or 2, history of diabetes mellitus or of any endocrine condition that would affect body weight, such as thyroid disease, pituitary abnormality, or Cushing's syndrome
2. Smoking during the past six months
3. Alcohol consumption of more than 2 drinks per day or the equivalent, episodic increased drinking (e.g., more than 2 drinks per day on weekends), or a history of alcohol abuse or dependency followed by any current use
4. Use of recreational drugs in the past 6 months
5. Use within the preceding six months of medications that affect appetite or body weight, such as estrogens or other hormones, thyroid medications (unstable dose within the preceding 6 months), systemic steroids, antidepressants (tricyclics, MAOIs, SSRIs), antipsychotics, lithium, anticonvulsants, appetite

suppressants or other weight-loss drugs, herbs for weight loss or mood, St. John's wort, ephedra, beta blockers

6. Pregnancy or intention to become pregnant during the study period
7. Unstable medical or psychiatric illness
8. Evidence of an eating disorder
9. Likely to be disruptive in group sessions
10. Already following a low-fat, vegan diet
11. Lack of English fluency
12. Inability to maintain current medication regimen
13. Inability or unwillingness to participate in all components of the study
14. Intention to follow another weight-loss method during the trial

### **3.5. Group Assignment**

Participants will be told that, if accepted, they will be assigned either to a Diet Group or a Control Group. Accepted volunteers will be assigned to these groups using a computer-generated random-number table. Because assignment will be done simultaneously within each replication, allocation concealment is unnecessary.

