## **6.2. Participant Flow Based on Power Analysis**

In order to accommodate this number of participants, baseline metabolic assessments will occur as follows for the first cohort:

January 6: 2 participants  
January 9-13: 10 participants  
January 17-20: 8 participants  
January 23-27: 10 participants  
January 30-Feb 3: 10 participants

The MR spectroscopy studies will be limited to 40 participants (20 per study arm) total. These evaluations will be scheduled during the above scheduled days.

The Diet Group sessions for the first cohort will be held for 16 weeks, from February 1 through May 17, 2017.

For the first cohort in 2017, the 16-week metabolic assessments will occur as follows:

May 18-19: 4 participants  
May 22-26: 10 participants  
May 30-June 2: 8 participants  
June 5-9: 10 participants  
June 12-15: 8 participants

For the second cohort, the assessment and intervention dates will be approximately one month later than those for the first cohort.

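### Concealment is waived because assignment is simultaneous, yet the first-cohort calendar still tests baseline two days after Diet Group classes begin

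*Protocol*

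**What the plan says.** Three parts of the protocol bear on the order of events.

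- **Enrolment (section 3.3).** "Those who satisfactorily complete the baseline assessments and 3-day dietary records will be enrolled in the study". Baseline testing therefore comes before entry to the study, and staff judge whether it was done satisfactorily.
- **Allocation (section 3.5).** "Accepted volunteers will be assigned to these groups using a computer-generated random-number table". The waiver follows: "Because assignment will be done simultaneously within each replication, allocation concealment is unnecessary". No other reason is offered. The section does not say when the list of people to be allocated is closed, or who applies the random table.
- **Calendar (section 6.2, first cohort).** The last baseline block is "January 30-Feb 3: 10 participants". The classes are dated as follows: "The Diet Group sessions for the first cohort will be held for 16 weeks, from February 1 through May 17, 2017". The final tests are introduced with "For the first cohort in 2017, the 16-week metabolic assessments will occur as follows", and run from "May 18-19: 4 participants" to "June 12-15: 8 participants".

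Section 6.2 places the second cohort about a month later, and section 6.1 says that later years will follow similar time frames. Exact dates are given for the first cohort only.

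**The concern.** Allocating a whole cohort at once protects against selection only if the cohort is already fixed when the random list is applied. If entry is still open for anyone at that moment, the person deciding whether a baseline was satisfactory may know which arm that participant is in. Participants cannot be blinded to a vegan diet with weekly classes versus no change, so sound allocation is one of the few protections available.

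The calendar suggests that entry is still open. The Diet Group has to be known when classes start on 1 February, but the last block of baseline tests is not finished until 3 February.

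There is a second consequence. Section 5.3 tests the change from baseline and also uses baseline values as covariates. A Diet Group baseline taken after the diet has begun is not a pre-treatment value, and only that arm is exposed to this.

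**Working it through.** **Inputs.** All dates and block sizes come from section 6.2, and the cohort size of 40 from section 6.1. The only added assumption is an even spread of slots within a block.

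**1. Reproducing the plan's own figures.**

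- Baseline slots: 2 + 10 + 8 + 10 + 10 = 40.
- Final slots: 4 + 10 + 8 + 10 + 8 = 40.
- Classes: 1 February to 17 May 2017 is 105 days. Both dates are Wednesdays, so 105 / 7 + 1 = 16 weekly sessions.

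The totals and the number of sessions agree with the plan.

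**2. Baseline tests against the first class.** The five baseline blocks cover 1, 5, 4, 5 and 5 weekdays, and each gives exactly 2 slots per day. In the block from 30 January to 3 February:

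- on or after 1 February: 3 days x 2 = 6 of 40 (15%);
- strictly after the first class day (2 and 3 February): 2 days x 2 = 4 of 40 (10%).

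With equal arms, about half of these would be Diet Group members, that is 2 to 3 people.

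The diet record could widen the gap. Section 3.3 has participants asked for the 3-day record at the baseline appointment. If it is filled in over the three days after the visit (an assumption), even the 30 January visits would be complete only on 2 February. All 10 in the last block would then miss the enrolment condition by 1 February.

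**3. What the two possible orders imply.**

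- *Everyone is allocated together by 1 February.* Assignment is simultaneous, but the last few are allocated before completing what section 3.3 requires for enrolment. Their baselines are measured and judged with the allocation already made. Simultaneity does not protect them, because entry was still open.
- *The last few are allocated after their own baseline.* Section 3.3 is respected, but assignment within the cohort is no longer simultaneous. The premise of the waiver is then false.

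No order of events satisfies sections 3.3 and 3.5 and the section 6.2 calendar together.

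**4. Final tests against the last class.**

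- 17 May to 18 May is 1 day; 17 May to 15 June is 29 days.
- 1 February to 18 May is 106 days, or 15.1 weeks; 1 February to 15 June is 134 days, or 19.1 weeks.
- Sixteen full weeks from 1 February is 24 May, so the last test is 22 days beyond that.
- If participants are tested in the same order both times, each baseline-to-final interval is 129 to 132 days, about 18.8 weeks.

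**The case against.** The strongest reply is that section 3.5 speaks of accepted volunteers and section 3.3 of enrolled ones, and the protocol never equates the two. All 40 could be accepted and randomised together on or before 1 February. This stands, and it means that a reader who infers that simultaneous allocation is impossible goes too far. It does not rescue the waiver. On that reading, a few baselines are taken and judged after allocation, which is the situation concealment exists to prevent.

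It can also be said that once the roster is truly locked and allocated in one step, little more is needed. That is right, and it is what the fix asks for. The protocol does not state the lock, and its calendar contradicts it.

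Other stronger readings are tempting but not supported:

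- *All change scores are contaminated.* The overlap concerns about 4 to 6 of 40 baselines, roughly half of them in the Diet Group and at most two days after the first class day. Tests on 1 February may even precede that day's class.
- *The same share applies to all six cohorts.* Exact dates exist for one cohort. Similar time frames, and a start about a month later, do not fix an overlap elsewhere.
- *Staff could use the exclusion for likely disruptiveness with allocation known.* Section 3.3 offers baseline appointments only to people who already meet the participation criteria, so that judgement comes earlier. What can overlap with allocation is the judgement that baseline was satisfactory.
- *The late final tests bias the comparison.* They apply to both arms and mirror the spread of the baseline tests. Luteal-phase timing for premenopausal women (section 3.6) may disturb the order, but nothing in the protocol points to imbalance between arms.

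**Conclusion.** The point holds as an internal contradiction. Section 3.5 waives concealment on one ground, and the first-cohort calendar, read with the enrolment rule in section 3.3, removes that ground.

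The size is modest: about 6 of 40 first-cohort baselines on 1-3 February, 4 of them after the first class day, and perhaps 2 to 3 in the Diet Group. These counts assume an even spread within the last block and equal arms. The dates alone establish only that baseline testing is still under way two days after classes begin. The counts also take the first class as the start of diet instruction; section 4.4 mentions individual meal-planning meetings but does not date them.

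The numbers are small, but the waiver is a general rule for every cohort and is wrong as written, so it should be corrected even if later calendars contain no overlap.

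The secondary point is one of labelling. Tests called 16-week are spread from 15.1 to 19.1 weeks after the first class, and from 1 to 29 days after the last.

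**What to change.** 1. Reconcile sections 3.3, 3.5 and 6.2 so that each cohort's roster is closed after its last completed baseline test and diet record, and before a single allocation and the first class. Use one term for the people who are allocated, and define it.
2. Delete the statement that concealment is unnecessary. In its place, state that the random list is applied once to the locked roster by someone not involved in screening or baseline assessment, and that nobody is added or removed afterwards.
3. In section 6.2, replace the 16-week label for the final tests with the actual window in weeks from the first class.

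The cost is protocol wording and a shift of a few calendar days in the first cohort, and in any other cohort planned with the same overlap. The sample size and the set of assessments do not change.

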### **3.6. Clinical Assessments**

The following determinations will be made at baseline and 16 weeks, except as noted:

#### **Assessments of Dietary Intake and Physical Activity**

**3-day dietary record.** A 3-day dietary record will be used to assess macro- and micronutrient intakes. Records will be analyzed using Nutrition Data System for Research software version 2016, developed by the Nutrition Coordinating Center (NCC), University of Minnesota, Minneapolis, MN, US, by a registered dietitian certified by the NCC. Random 24-hour dietary recalls will be conducted by registered dietitians to determine compliance but will not be part of the final nutrient analysis.

The **International Physical Activity Questionnaire** short form assesses recent physical activity patterns. The method is highly reliable; an assessment of test-retest repeatability produced a correlation of 0.8. (**Appendix 7**)

#### **Assessments of Physical Health, Weight, and Metabolism**

**General status, symptoms, and medication accounting.** Participants will be asked to report changes in their health and medication use.

**Height.** Height will be measured at baseline (only) with participants standing barefoot with their backs to a wall-mounted stadiometer and heels against the wall, recorded to the nearest 0.5 cm.

**Body weight.** With participants wearing light, indoor clothing but without shoes, body weight will be measured to the nearest 0.1 kg, using a digital scale. Body weight will also be assessed at each weekly group session for the Diet Group, but only data from weeks 0, 8, and 16 will be included in the analysis.

**Comprehensive Metabolic Panel.** These values will be evaluated at baseline only.

**Serum cholesterol and triacylglycerol concentrations and hemoglobin A1c** will be measured using standard methods.

The following measures will be assessed at weeks 0 and 16:

**Glucose Tolerance and Insulin Sensitivity.** An oral glucose tolerance test will be performed for three hours after an overnight fast. (Matsuda 1999) **Resting Energy Expenditure (REE).** Participants will be asked to report to the laboratory within 60 minutes of waking and after a 12-hour fast. Following 30 minutes of quiet rest in a dimly lit room, pulse, respiratory rate, and body temperature will be measured. REE will be measured for 20 minutes through indirect calorimetry (Cosmed Quark RMR, Chicago, IL) utilizing a ventilated hood system. The laboratory temperature will be maintained at 23 degrees C throughout, and precautions will be taken to minimize any disturbances that could affect the metabolic rate.

For premenopausal women, measures will be timed so as to occur in the luteal phase of the menstrual cycle.

**Postprandial metabolism** (thermic effect of food, TEF). After the REE determination, participants will be given a 720-kilocalorie test meal (Sustacal, Mead Johnson, Evansville, IN) to be ingested within 10 minutes. Metabolic rate will be measured in the same manner as above for 30 minutes at 2 and 4 hours postingestion.

**Body Composition.** Body composition will be measured by dual energy x-ray absorptometry (Lunar iDXA, GE Healthcare; Madison, WI) with Encore® 2005 v.9.15.010 software. The iDXA can measure body composition with low X ray exposure and short scanning time. The iDXA unit will be calibrated daily using the GE Lunar calibration phantom, and a trained operator will perform all scans following standard protocol for participant positioning. The iDXA is equipped with the CoreScan module (GE Healthcare, Madison, WI), which can also provide an estimate of visceral adipose tissue volume and mass.

**Microbiome.** Microbiome will be assessed through uBiome SmartGut microbiome screening test, by using advanced DNA sequencing to determine specific bacteria and other microorganisms. Study participants will be given their 1st kit at recruitment and a 2nd kit during the last week of the study. Study participants will collect their stool sample and perform the uBiome test at home. They will then bring their packaged sample to the clinic to be shipped in one shipment to uBiome for analysis. Results will be sent to

Digestive Center for Wellness, where [name] will interpret the results. With this, we are able to track any changes in microbiome related to dietary changes.

**Endothelial function.** Endothelial function will be assessed with the use of the itamar EndoPAT. EndoPAT quantifies the endothelium-mediated changes in vascular tone, elicited by a 5-minute occlusion of the brachial artery (using a standard blood pressure cuff). When the cuff is released, the surge of blood flow causes an endothelium-dependent flow mediated dilatation. The dilatation is captured by EndoPAT as an increase in the PAT signal amplitude. The PAT signal used in the EndoPAT is measured from the fingertip by recording finger arterial pulsatile volume changes. Results of the 15-minute test are automatically calculated and an EndoScore is generated, which indicates the present state of endothelial health. We will assess the endothelial function at baseline, and in response to a 16-week low-fat plant-based dietary intervention.

**Intramycellular and Hepatic Lipid Content.** A subset of participants will be selected for MR spectroscopy studies quantifying hepatic lipid and/or intramycellular and/or contents in order to provide data regarding possible causal relationships between dietary changes, ectopic lipid, and insulin sensitivity. Selected individuals with varying degrees of insulin-resistance in both groups will be assessed before and after the intervention period. These MRS studies will take place at the Magnetic Research Center at Yale University School of Medicine, New Haven, CT.

Intramycellular and hepatic lipid contents will be measured using  $^1\text{H}$  MRS at 4T (Bruker). After safety procedures including completion of the Yale Magnetic Research Center Safety Questionnaire, changing into scrubs and passing through the metal detector, the participants will be positioned on their back on the bed, which slides into the MRS instrument. For the leg lipid measurements the right leg will be positioned in a holder with the calf muscle over a receiver coil.

Muscle lipid content will be measured in the soleus muscle using an 8.5-cm diameter circular  $^{13}\text{C}$  surface coil with twin, orthogonal circular 13-cm  $^1\text{H}$  quadrature coils. The probe will be as tuned and matched and scout images of the lower leg will be obtained to ensure correct positioning of the participant and to define an adequate volume for localized shimming using the FASTMAP procedure. The measurement will take approximately 30 minutes.

After the lipid measurements in the leg a receiver coil embedded in a plastic plate will be positioned on the side of the abdomen over the liver and strapped in place with velcro straps. The position of the coil will be confirmed with MR images and the location of the lipid measurement within the coil will be determined from these MR images. Liver triglyceride content will be measured by  $^1\text{H}$  respiratory-gated STEAM spectroscopy in a  $15 \times 15 \times 15\text{-mm}^3$  voxel. Acquisition will be synchronized to the respiratory cycle and triggered at the end of expiration. A water-suppressed lipid spectrum and a lipid-suppressed water spectrum will be acquired in three different locations of the liver to account for liver inhomogeneity. A minimum of three spectra will be acquired for each participant and the total lipid content will be averaged and calculated. In addition,

hepatic lipid content will be corrected for transverse relaxation, using the transverse relaxation times of 22 ms for water and 44 ms for lipid. These MRS measurements will take approximately 30 minutes.

